## Abstract

**Background:**

Metabolic dysfunction–associated steatotic liver disease is highly prevalent in adults with type 2 diabetes, and advanced fibrosis is its strongest prognostic marker. However, existing noninvasive tools may underperform in diabetes care and are inconsistently used in practice.

**Objective:**

This study aims to evaluate the feasibility, usability, and preliminary diagnostic effectiveness of FibroX, an explainable artificial intelligence tool for identifying metabolic dysfunction–associated steatotic liver disease–associated advanced fibrosis in adults with type 2 diabetes.

**Methods:**

This 12-month health care provider–level randomized crossover pilot trial will enroll at least 36 primary care clinicians managing adults with type 2 diabetes. Participants will complete 2 simulated care periods: one with FibroX-enabled care and one with usual care, separated by a 1-week washout. FibroX generates individualized advanced fibrosis risk estimates from routine clinical data, provides guideline-aligned triage categories, and displays case-level explanatory outputs using Shapley Additive Explanations. FibroX is an investigational tool and is not currently used in routine clinical practice. Primary outcomes are feasibility and usability, while secondary and exploratory outcomes include workflow efficiency, preliminary diagnostic performance, and implementation measures.

**Results:**

Institutional review board approval has been obtained. The protocol was registered on ClinicalTrials.gov (NCT07305324) on December 1, 2025. At the time of submission, recruitment had not yet begun. The study is currently unfunded. Preparatory activities, including platform development and case validation, are ongoing. Recruitment is expected to begin in June 2026, with primary completion anticipated in May 2027 and results expected to be available in late 2027.

**Conclusions:**

This pilot study will provide preliminary evidence on the feasibility, usability, and diagnostic performance of an explainable artificial intelligence tool for fibrosis risk stratification in diabetes care and will inform the design of a future larger trial.

**Trial Registration:**

ClinicalTrials.gov NCT07305324; https://clinicaltrials.gov/study/NCT07305324

**International Registered Report Identifier (IRRID):**

PRR1-10.2196/90456

## Introduction

### Background

Metabolic dysfunction–associated steatotic liver disease (MASLD) is highly prevalent and clinically consequential among people living with type 2 diabetes (T2D). Population studies indicate that steatosis and progressive fibrosis affect a large proportion of adults with T2D, with MASLD prevalence approaching 70% in some cohorts, and advanced fibrosis (stage ≥F3) conferring markedly elevated risks of liver-related events and cardiovascular morbidity and mortality [1-4]. Advanced fibrosis is the strongest prognostic marker in MASLD and is associated with 2 to 3-fold higher liver-related and cardiovascular mortality in diabetes populations [4,5]. Recent diabetes-focused guidance has therefore emphasized that adults with prediabetes or type 2 diabetes are a priority population for structured noninvasive fibrosis risk stratification rather than opportunistic case finding alone [2,3]. However, real-world implementation in primary care and diabetes clinics remains inconsistent, leading to missed opportunities for early intervention [1-4].

Current approaches to fibrosis assessment rely on a mix of laboratory-based composite scores (eg, the Fibrosis-4 Index [FIB‑4] and nonalcoholic fatty liver disease fibrosis score) and imaging modalities (eg, vibration-controlled transient elastography [VCTE] and magnetic resonance elastography) [6-8]. While elastography provides strong diagnostic performance, it requires dedicated equipment and trained personnel, limiting availability; meanwhile, fixed-formula laboratory scores can underperform in T2D populations where metabolic and inflammatory profiles differ, and they do not capture complex, nonlinear relationships among routinely collected clinical variables [9-12]. Liver biopsy, although a reference standard, is invasive, subject to sampling variability, and not suitable for screening at scale [6]. Consequently, many individuals with T2D and advanced fibrosis remain undetected until late disease stages, when therapeutic options are limited and outcomes are poorer [7,13]. In real-world practice, these pathways often depend on simplified cutoffs followed by second-line elastography, which can leave many at-risk patients in indeterminate categories and create access and workflow barriers in primary care [4,14,15].

Explainable artificial intelligence (AI) offers a path to more accurate, transparent, and workflow-compatible decision support in diabetes care. Prior work has shown that machine learning models leveraging routinely available data can improve discrimination for high-risk MASLD and fibrosis outcomes, while post hoc explanation methods enhance interpretability and clinician trust [16-19]. Recent studies in liver disease and other clinical prediction settings have increasingly used explainable machine learning approaches to move beyond black-box risk estimates and provide patient-level feature attribution that may support clinician interpretation and adoption [20-22].

Building on this foundation, FibroX was developed to estimate individualized risk of advanced fibrosis (≥F3) using common clinical inputs (age, aspartate aminotransferase [AST], alanine aminotransferase [ALT], platelets, hemoglobin A_1c_ [HbA_1c_], BMI, creatinine or estimated glomerular filtration rate), with dual-threshold triage bands aligned to guidelines (rule out, indeterminate to elastography, and rule in to hepatology referral) and Shapley Additive Explanations (SHAP) to surface the features most responsible for each prediction [17,18]. In prior work, FibroX was derived using an explainable Extreme Gradient Boosting framework applied to population-based National Health and Nutrition Examination Survey data and subsequently evaluated in external biopsy-confirmed MASLD cohorts. Across these earlier evaluations, FibroX showed better discrimination for advanced fibrosis than conventional noninvasive scores such as FIB-4 and was also associated with prognostic stratification for longer-term outcomes. However, FibroX remains investigational, and its feasibility, usability, and influence on clinician decision-making have not yet been prospectively assessed in a clinical workflow context [15-18].

### Study Objectives and Rationale

This pilot aims to evaluate the feasibility, usability, and preliminary effectiveness of FibroX as an explainable AI decision support tool for detecting MASLD-associated advanced fibrosis in adults with T2D during simulated clinical encounters. Specifically, we aim to (1) assess the primary pilot end points of feasibility and usability in diabetes-focused primary care workflows using validated instruments, (2) estimate secondary outcomes related to workflow efficiency and preliminary diagnostic performance for advanced fibrosis, and (3) explore adoption and implementation metrics using the Reach, Effectiveness, Adoption, Implementation, and Maintenance framework, including guideline-concordant triage and net reclassification improvement (Figure 1).

If FibroX proves feasible and acceptable and improves diagnostic discrimination, it could help operationalize guideline-concordant triage, reduce missed diagnoses, and inform equitable MASLD screening strategies in diabetes care [1-4,10,12,13,16].

**Figure 1 figure1:**
[figure not shown]
Schematic of FibroX inputs, explainable outputs, and clinician actions in the simulated diabetes care workflow. ALT: alanine aminotransferase; AST: aspartate aminotransferase; AUROC: area under the receiver operating characteristic curve; eGFR: estimated glomerular filtration rate; HbA_1c_: hemoglobin A1c; MASLD: metabolic dysfunction–associated steatotic liver disease; SHAP: Shapley Additive Explanations; T2D: type 2 diabetes.

## Methods

### Trial Design and Oversight

We will conduct a 12-month, health care provider–level, randomized, 2‑period crossover simulation trial to evaluate the feasibility, usability, and preliminary effectiveness of FibroX, an explainable AI decision support tool for detecting MASLD‑associated advanced liver fibrosis (≥F3) in adults with T2D. Because FibroX is not currently used in routine clinical care, this study evaluates the tool in a simulated clinical environment. Each clinician serves as their own control (FibroX-enabled care vs usual care), separated by a 1-week washout. Distinct, nonoverlapping simulation case sets will be used in each study period, such that clinicians will not evaluate the same cases across periods, reducing case-recall bias and minimizing carryover related to prior exposure. The study involves no patient enrollment and uses deidentified or synthetic cases. Oversight is by the principal investigator and study steering team; a formal Data Monitoring Committee is not required given the minimal risk.

### Study Setting

Health care provider participants will be recruited from Yale-affiliated diabetes and primary care clinics and participating federally qualified health centers. Simulations are delivered via a secure, web-based platform designed to replicate an electronic health record (EHR)–like interface. Each simulated case presents standardized clinical information, including patient demographics, laboratory values, and relevant clinical notes. Participants review cases sequentially and make diagnostic and management decisions within this interface. In the FibroX-enabled condition, additional outputs—including predicted risk of advanced fibrosis, guideline-aligned triage categories, and SHAP-based feature explanations—are displayed alongside standard clinical data.

### Participants

This pilot will enroll licensed primary care clinicians, including physicians, nurse practitioners, and physician assistants. Inclusion criteria require health care providers to have ≥0.5 full-time equivalent dedicated to adult diabetes care at participating sites, the ability to complete 2 simulation periods, and provision of informed consent. Exclusion criteria include prior participation in any FibroX usability or validation studies, exclusive practice in pediatrics or nondiabetes specialty areas, or inability to complete all study procedures. Participating clinicians are expected to have varying levels of clinical experience, reflecting real-world primary care practice, but all are required to have active involvement in the management of adult patients with T2D to ensure familiarity with relevant clinical workflows and decision-making. Participants will be recruited through email invitations and departmental announcements across Yale-affiliated primary care and diabetes clinics, as well as participating federally qualified health centers. Recruitment will target clinicians with active involvement in the management of adults with T2D, with participation on a voluntary basis.

The simulation case library will comprise adult patients (aged ≥18 years) with T2D and at least one additional MASLD risk factor (eg, obesity, dyslipidemia, and hypertension). Each case must have a ground-truth fibrosis stage determined by liver biopsy or expert consensus based on VCTE. To ensure fidelity to real-world clinical presentation, cases will include complete routine clinical data such as age, AST, ALT, platelet count, HbA_1c_, BMI, and creatinine or estimated glomerular filtration rate, along with relevant clinical notes. The simulation case library will be developed using deidentified or synthetic cases derived from representative clinical datasets and prior cohorts, with case selection designed to capture a range of fibrosis risk profiles and clinical presentations. Cases will be curated to ensure clinical realism, balanced representation across fibrosis stages, and inclusion of all variables required for FibroX and comparator assessments.

### Interventions

The intervention arm, known as FibroX-enabled care, will use a simulated EHR-like interface delivered through a secure web-based platform that mirrors the presentation of routine outpatient clinical information. Participants will review standardized simulated cases containing patient demographics, relevant clinical history, laboratory data, and clinical notes. Within this interface, FibroX-enabled care will display key predictive and explanatory information at the point of decision-making. This will include individualized FibroX risk estimates for advanced fibrosis generated using routinely available clinical data. Crucially, the interface presents dual-threshold triage bands aligned with established clinical guidance, classifying patients into 3 actionable categories: rule out, indeterminate (with a pathway to VCTE or other noninvasive testing), and rule in (with a pathway to hepatology referral). In addition, the interface presents case-level SHAP outputs that display the relative contribution of individual clinical variables (eg, age, AST, ALT, platelet count, HbA_1c_, BMI, and kidney function) to the predicted risk of advanced fibrosis. These explanations are presented in a structured visual format, such as ranked feature contributions, alongside the risk estimate and triage category to support clinician interpretation at the point of decision-making. By providing case-level explanations of the key drivers of predicted risk, these SHAP-based outputs are intended to support clinician interpretation of the model’s recommendations, increase confidence in triage decisions, and facilitate more consistent application of guideline-concordant referral pathways compared with usual care, where risk estimation is often implicit and variable.

The comparator arm, designated as usual care, will present the same standardized clinical case information within the simulated EHR-like interface but without FibroX risk estimates, SHAP explanations, or AI-based triage support. Participants in this arm will make diagnostic and management decisions based on routine clinical judgment alone. Optional access to a basic FIB-4 calculator will be provided, reflecting common clinical practice for noninvasive fibrosis risk stratification. FIB-4 is a widely used blood-based fibrosis score derived from age, AST, ALT, and platelet count to estimate the likelihood of advanced fibrosis [23].

### Outcomes

The primary end points of this pilot study are the feasibility and usability of FibroX-enabled care within diabetes-focused clinical workflows. Feasibility will be assessed using recruitment and study completion rates, with prespecified targets of enrolling at least 70% of eligible clinicians and achieving a completion rate of at least 85% among enrolled participants. Completion will be defined as participants completing both simulation periods, including all assigned cases and postperiod surveys. Participants who do not complete both periods or required assessments will be classified as incomplete. Usability will be evaluated using the System Usability Scale (SUS), with a prespecified success threshold of 70 or higher.

Secondary end points include workflow efficiency and preliminary diagnostic performance. Workflow efficiency will be assessed by median time per case, with an anticipated threshold of 3.5 minutes or less. Preliminary diagnostic performance outcomes will include sensitivity, specificity, and the area under the receiver operating characteristic curve for the detection of MASLD-associated advanced fibrosis. Calibration will be examined using intercept, slope, and graphical assessment of predicted versus observed risk.

Exploratory end points will include clinician trust and cognitive workload, assessed using the AI trust scale and National Aeronautics and Space Administration Task Load Index (NASA-TLX), respectively, as well as implementation-related outcomes, including the proportion of guideline-concordant referrals and net reclassification improvement. Qualitative debrief interviews will further explore clinician understanding, interpretability, and perceived usefulness of the SHAP-based explanations, including how these outputs influence decision-making and trust in the model. These measures are intended to provide pilot estimates and inform the design, end point selection, and sample size considerations for a future definitive trial.

At a high level, this pilot will be considered successful if predefined feasibility and usability thresholds are met, including adequate recruitment and completion rates and a SUS score of 70 or higher, alongside signals of acceptable workflow efficiency and improved or comparable diagnostic performance relative to usual care. These criteria are intended to determine whether progression to a larger, real-world trial is justified.

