### Data Collection Methods

The platform automatically logs case navigation, decisions, timestamps, and use of FibroX features and overrides. Clinicians will not receive case-level performance feedback during either simulation period. Feedback, if provided, will be deferred until completion of the study period to minimize within-period learning effects. Surveys (SUS, AI trust, and NASA‑TLX) are administered electronically at the end of each period. Qualitative debriefs are audio-recorded and transcribed for thematic analysis. Completeness checks and range validations occur at ingestion.

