Feasibility outcomes, including recruitment and completion rates, will be summarized descriptively with proportions and 95% CIs. Usability and trust scores from the SUS and AI trust scale will be analyzed using paired *t* tests or Wilcoxon signed-rank tests, depending on distributional assumptions. Cognitive workload scores from NASA-TLX will be compared similarly. Subgroup analyses will explore whether diagnostic performance varies across diabetes-related characteristics such as HbA_1c_, BMI, and duration of diabetes, using interaction terms in mixed-effects models. Missing data are expected to be minimal; if more than 5% of survey data are missing, multiple imputation under a missing-at-random assumption will be applied, with sensitivity analyses conducted using complete-case data. All statistical tests will be 2-sided with an α level of .05, and analyses will be performed using the R (R Foundation for Statistical Computing) or Python (Python Software Foundation) statistical packages.

To aid interpretation of the crossover design, sequence, period, and potential carryover effects will be explicitly examined. Sequence effects (AB vs BA) will assess whether the order of exposure to FibroX influences outcomes. Period effects will evaluate whether outcomes differ between the first and second study periods, independent of the intervention, which may reflect learning or temporal effects. Potential carryover effects will be explored by assessing interaction terms between intervention and study period and by comparing outcomes across sequences; a significant difference by sequence or interaction with period would suggest residual carryover. If meaningful carryover effects are detected, sensitivity analyses restricted to first-period data will be performed.

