**Assessments**														
	**Feasibility outcomes**													
		Decision time (workflow efficiency)					✓				✓			
		Usability (SUS^j^ score)					✓				✓			
		Trust in AI^k^ (AI trust scale)					✓				✓			
		Cognitive workload (NASA-TLX^l^)					✓				✓			

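### Workflow efficiency is judged only by an absolute 3.5-minute median, with no condition named and no reference to usual care, so meeting or missing it does not show whether FibroX slows or speeds clinicians

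*Protocol article*

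**What the plan says.** The Outcomes section makes workflow efficiency a secondary end point and defines it in one sentence: "Workflow efficiency will be assessed by median time per case, with an anticipated threshold of 3.5 minutes or less". The condition is not named, no basis for 3.5 minutes is given, and no difference or margin against usual care is set.

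The closing paragraph of the same section brings efficiency into the pilot's success rule. Besides the recruitment, completion and System Usability Scale (SUS) thresholds, it asks for success "alongside signals of acceptable workflow efficiency and improved or comparable diagnostic performance relative to usual care", and adds: "These criteria are intended to determine whether progression to a larger, real-world trial is justified".

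The design supplies a control for time. Trial Design and Oversight says "Each clinician serves as their own control (FibroX-enabled care vs usual care), separated by a 1-week washout", Data Collection Methods says "The platform automatically logs case navigation, decisions, timestamps, and use of FibroX features and overrides", and Table 1 ticks decision time in both intervention periods.

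The Statistical Analysis section describes comparisons for accuracy, net reclassification, SUS and trust. It also covers the exploratory workload score: "Cognitive workload scores from NASA-TLX will be compared similarly". It does not name time per case.

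**The concern.** Time per case in a simulated record depends on how long and hard the cases are, how the interface is laid out and how fast each clinician reads. An absolute median mixes all of these with whatever FibroX adds or saves. The usual-care period measures the same clinicians on the same platform, and the criterion does not use it.

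FibroX places a risk estimate, a triage band and an explanatory display beside the same case information, so extra reading time is a plausible effect. A fixed ceiling cannot show it when usual care lies well below the ceiling. Nor can it show a gain when usual care lies above. At stake is the efficiency signal that the sponsor will weigh in deciding whether a larger trial is justified.

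**Working it through.** **The plan's own figure.** The article gives no derivation, baseline time, SD or margin for 3.5 minutes, so there is nothing to reproduce. The Sample Size section concerns accuracy only. Its count agrees with its inputs (36 × 32 = 1152 and 40 × 32 = 1280, against the stated 1150 to 1280) but says nothing about time.

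**Step 1: slowdown compatible with meeting the figure.** Take 3.5 minutes as a limit on the FibroX median and let T be the usual-care median. T is not in the article, so a range is assumed. The largest FibroX to usual-care ratio that still meets the figure is 3.5/T.

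| Assumed T (min) | 3.5/T | Slowdown allowed |
|---|---|---|
| 1.5 | 2.33 | +133% |
| 2.0 | 1.75 | +75% |
| 2.5 | 1.40 | +40% |
| 3.0 | 1.17 | +17% |
| 3.5 | 1.00 | none |

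**Step 2: the reverse error.** If T is above 3.5, FibroX can be faster and still miss. With T = 4.5 and FibroX at 3.7, the ratio is 3.7/4.5 = 0.82. That is 18% faster, yet 3.7 exceeds 3.5.

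**Step 3: would the crossover data show it?** A Monte Carlo check used 36 clinicians and 1000 runs per scenario. All its settings are assumptions:
- 16 cases per condition and log-normal times;
- log-scale SDs of 0.3 between clinicians, 0.2 for clinician by condition and 0.5 within clinician;
- no period or case effects;
- a paired t test on log clinician medians (critical value 2.03), with the ceiling applied to the overall FibroX median.

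| Usual care to FibroX (min) | True change | Result | Share of runs |
|---|---|---|---|
| 1.5 to 3.0 | +100% | meets 3.5 and significantly slower | 0.99 |
| 2.0 to 3.0 | +50% | meets 3.5 and significantly slower | 0.99 |
| 2.5 to 3.0 | +20% | meets 3.5 and significantly slower | 0.93 |
| 3.0 to 3.3 | +10% | meets 3.5 and significantly slower | 0.35 |
| 5.0 to 4.0 | −20% | misses 3.5 and significantly faster | 0.98 |

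Under these settings, the paired data usually reveal what the ceiling does not.

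**Step 4: precision of a ratio.** The 95% half-width on the log scale is 2.03 × SD/√36, where SD is that of the within-clinician log-time difference (assumed 0.3 to 0.5).
- SD 0.3: 2.03 × 0.3/6 = 0.10, so the upper limit is about 11% above the estimate and the lower about 10% below.
- SD 0.5: 2.03 × 0.5/6 = 0.17, so about 18% above and 16% below.

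A pilot of 36 clinicians can therefore estimate the ratio usefully.

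**The case against.** The strongest reply is that 3.5 minutes is not a binding gate. The article calls the recruitment, completion and SUS targets prespecified, but this figure only anticipated. The success rule is introduced as high-level, asks for signals and does not repeat 3.5 minutes. This stands: a reader might infer that FibroX automatically passes or fails on 3.5 minutes, and the text does not say so. But no other definition of acceptable efficiency is given, so the figure is what the signal will naturally be read against.

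Second, the closing reference to usual care in the success rule might be meant to cover efficiency as well as diagnostic performance. That reading is possible but less natural. If it is the intended one, the success rule and the end point definition do not match, and the same edit is needed.

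Third, an analysis plan not seen here may compare times, and the Statistical Analysis section does promise to examine sequence, period and carryover effects on outcomes in general. It would be wrong to conclude that no comparison is planned. The point rests on the criterion, which the article itself fixes without the comparator.

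Fourth, a time ceiling answers a fair feasibility question (does the tool fit a usable time budget?), and a slower decision may be worth having if accuracy rises. Both are true. They are reasons to keep 3.5 minutes as a benchmark and to state an acceptable slowdown; they do not justify leaving out the comparison.

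**Conclusion.** The point holds for a secondary end point that feeds the success rule. As defined, meeting or missing 3.5 minutes says nothing about the direction of the FibroX effect on time. Taken as a limit on FibroX time, it allows up to +75% if usual care takes 2.0 minutes and up to +17% if it takes 3.0, and it can be missed at 3.7 against 4.5 minutes.

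The size rests on assumed usual-care medians and, for the Monte Carlo and precision figures, on assumed SDs. The slowdown case needs a usual-care median below 3.5 minutes. Nothing in the article shows whether that is likely, or that FibroX will in fact slow anyone down.

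A reader might also infer that one median will be pooled over both conditions. The article does not say this; it only leaves the condition unnamed. The primary end points, feasibility and usability, are untouched.

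**What to change.** Amend the Outcomes section in three places.

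1. State that 3.5 minutes applies to the FibroX-enabled condition and is reported as a descriptive benchmark only.
2. Define the efficiency measure, for example: *Workflow efficiency is the within-clinician ratio of time per case, FibroX-enabled to usual care, estimated from a mixed model on log time with condition, period and sequence as fixed effects and clinician and case as random effects, with a 95% CI.* The period and case terms matter because the two periods use different case sets.
3. Have the sponsor prespecify, before recruitment, the largest slowdown it would still call acceptable, and judge the efficiency signal in the success rule on the ratio against that margin. The 3.5-minute benchmark should not remain a second condition in that rule; otherwise a tool that is faster than usual care could still fail.

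The cost is one extra model on times the platform already logs, agreement on a margin, and a success signal that may be harder to meet. Recruitment had not begun at submission, so all of this can be fixed before data exist.
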